# **ABSTRACT**

# **Background:**

Gaze stability exercise is a medical procedure for persons with unilateral vestibular disturbances such as vestibular neuritis or persons who have had tumors of their 8^th^ nerve. They are a crucial part of the vestibular dysfunction rehabilitation protocols in health centers. These activities which involve turning one's eyes at different angles while having their eyes focused on an optotype are aimed at helping improve the vestibular ocular reflex (VOR), visual acuity during head movements and also reducing vertigo and dizziness.

# **Study aim**:

This review will be establishing the effectiveness of applying gaze stability with balance exercises procedure among participants who are suffering vertigo due to vestibular neuritis.

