## **1.4 Objectives**

This literature aims to assess whether conducting gaze stability with balance exercises has an improvement influence on balance and reducing falling incidence. Moreover, to study the impact of applying combination of gaze stability and balance exercises to improve activities of daily living in patients suffering from vertigo with vestibular neuritis in Saudi Arabia.

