# **2 METHODOLOGY**

## **2.1 Study design**

This research is experimental with Pre-post cohort design, Pilot clinical trial, by using telerehabilitation.

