### **2.2.1 Inclusion/exclusion criteria**

A convenience volunteers of middle-aged adults of 40-59 years old are diagnosed with vestibular neuritis and vertigo. Participants should not be either with a previous history of neurological diseases or brain surgery affecting equilibrium. Both male and female are cognitively intact. Subjects with medical issues, e.g., hypertension and diabetes, are undertaking medication regularly. Independent participants or those requiring reasonable assistance, but with balance disturbance in daily living activities and transferring, having Berg Balance Scale between 21-56 are included in the study.

However, subjects with the inability to follow instructions or completely dependent on the assistive device during mobility have been eliminated from the study. Participants with chronic dizziness diagnosed specifically with benign paroxysmal positional vertigo (BPPV), migraine-associated vertigo, or Meniere's disease are excluded. The research will be applied locally in Saudi Arabia, and all participants will sign a consent form approved by the Ethics Committee of King Saud University.

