## **2.3 Sample size**

Twenty convenient volunteers of middle-aged adults of 40-59 years old (n=20) are diagnose with vestibular neuritis and vertigo. The sample size is the same as previous studies (Roh and Lee, 2019).

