## **2.4 Intervention**

The gaze stability exercises (GSEs) and balance exercises (BE) are described by Roh& Lee (2019) and Khanna& Singh (2014), respectively. This research is reconstructed by combining two forms of exercises (GSEs)& (BE). Participants with vestibular neuritis and vertigo will be practicing a combination of gaze stability exercise (GSEs) and balance exercises (BE).

Gaze stability exercises are included in five phases: eyeball movement, saccadic eye movement, pursuit eye movement, vengeance eye movement, and vestibular-ocular reflex exercise (figure 1) (Appendix 2) (Roh and Lee, 2019). The eyeball exercise moves the eyes to a different direction slowly while they are closed to the left and right, up and down, rotation movements (Roh and Lee, 2019). The saccadic eye movement exercise moves the eyes as quickly as possible between the stationary points with a fixed head (Roh and Lee, 2019). The pursuit eye movement exercise by tracking slowly moving target with the eyes without moving head (Roh and Lee, 2019). The vergence eye movement exercise includes tracking the moving target from 5 cm close to eye level to as far as possible, both backward and forward (Roh and Lee, 2019). The vestibular-ocular reflex exercise keeps the eyes on the fixed point while moving the head from left to right (Roh and Lee, 2019). Gaze stability exercises will be performed while patients are seated, and each exercise lasts for 30 seconds.

Balance exercises, both static and dynamic with or without closing eyes, are recommended to improve postural stability (Khanna and Singh, 2014). In the first two weeks, patients will perform balance exercises with opening eyes, and then in the next couple of weeks, participants will do the same exercises with closing eyes (table 1) (Appendix 1). It involves standing on a firm surface with feet apart, heel stand, toe stand, marching on a firm surface, semi tandem stand, walking forward and backward with a normal support base (Khanna and Singh, 2014).

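### The protocol aims to establish effectiveness, but one uncontrolled group measured before and after four weeks can show only change, not an effect of the exercises

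*Protocol*

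**What the plan says.** **Aim.** The abstract's study aim is causal: "This review will be establishing the effectiveness of applying gaze stability with balance exercises procedure". Section 1 (Background Information) also speaks of effectiveness. Section 1.4 (Objectives) asks whether "conducting gaze stability with balance exercises has an improvement influence on balance and reducing falling incidence", and then refers to the impact of the combination on activities of daily living.

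**Design.** Section 2.1 states: "This research is experimental with Pre-post cohort design, Pilot clinical trial, by using telerehabilitation". Section 2.4 gives every participant the same programme: "Participants with vestibular neuritis and vertigo will be practicing a combination of gaze stability exercise (GSEs) and balance exercises (BE". Single-arm is not the protocol's own term, but it follows from these two sections. The two groups mentioned in the schedule in Section 2.4 are types of exercise, not groups of patients.

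**Measurement and test.** Section 2.5 places one assessment before treatment and one at the end of four weeks. Section 2.6 compares the two by paired t-test on each of the three scales (A-ABC, BBS, Katz ADL), with significance at p<0.05. There is no run-in and no repeated baseline.

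**Eligibility.** Section 2.2.1 says: "A convenience volunteers of middle-aged adults of 40-59 years old are diagnosed with vestibular neuritis and vertigo". It sets neither a minimum nor a maximum time since onset.

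**The concern.** The null hypothesis of a paired t-test is that the mean score does not change between the two assessments. The aim and objectives need a different null: that the exercises have no effect. The two coincide only if untreated patients would not change at all over four weeks. Nothing in the protocol supports that assumption, and nothing collected under it could test it.

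Recovery, familiarity with the tests and expectation would all add to the mean change. If the net background change is an improvement, the error favours the programme. An analysis plan written later cannot remove it, because the comparison that is needed is not in the data.

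The protocol's own literature review shows why this matters. Section 1.2 supports combining the exercises by citing a study that compared the combination with each component alone. It also reports a systematic review that found the therapy less effective than conservative or medical treatment. Before-after change in one group can neither confirm the advantage of the combination nor answer the unfavourable comparison.

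**Working it through.** **The plan's own figure.** Section 2.3 sets n=20 by matching an earlier study. It gives no effect size, SD or power, so 20 cannot be re-derived. The point here does not depend on disputing it.

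**Inputs.**
- n=20 (Section 2.3), so 19 degrees of freedom.
- Alpha 0.05 (Section 2.6). Sidedness is not stated; two-sided is assumed.
- True effect of the exercises: zero, by construction.
- Background improvement over four weeks: d, in SDs of the change score. The protocol gives no value, so a range is shown.

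**Chance of p<0.05 when the exercises do nothing.** The paired t statistic follows a noncentral t distribution with 19 df and noncentrality d × √20 = 4.472 × d. The two-sided critical value is 2.093.

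| Assumed background improvement d | Noncentrality | Chance of p<0.05 |
|---|---|---|
| 0 | 0 | 5% |
| 0.2 | 0.894 | 14% |
| 0.3 | 1.342 | 25% |
| 0.4 | 1.789 | 40% |
| 0.5 | 2.236 | 56% |
| 0.8 | 3.578 | 92% |
| 1.0 | 4.472 | 99% |

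The smallest observed mean change that reaches significance is 2.093 / √20 = 0.47 SD of the change score.

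**What a concurrent control would do.** With 10 patients per arm, the same background improvement in both arms and a t-test on change, 100,000 simulated trials per setting gave p<0.05 in 4.9% to 5.0% for d = 0, 0.2, 0.5, 0.8 and 1.0. The background change cancels. Such a trial would be small, though. Its power for a true between-arm difference of 0.5, 0.8 or 1.0 SD is about 20%, 43% or 61% (normal approximation). For 80% power the number per arm is 2 × (1.960 + 0.842)² / difference² = 15.70 / difference², rounded up: 63, 25 or 16.

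**Eligibility.** The only mention of chronicity is "Participants with chronic dizziness diagnosed specifically with benign paroxysmal positional vertigo (BPPV), migraine-associated vertigo, or Meniere's disease are excluded". It removes other diagnoses and does not restrict how long ago the neuritis began. The balance criterion, "having Berg Balance Scale between 21-56 are included in the study", does not either. Recent cases with recovery ahead of them and long-standing cases with little left can both enter, so the protocol does not even fix which part of the range above is relevant.

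**The case against.** **The table is generic.** The same figures would hold for any uncontrolled pre-post study of 20. They show that a paired t-test detects change, not how much background change there is here. This stands. The protocol does not mention spontaneous recovery, and its size in this disease would have to come from outside the documents. The figures are an illustration under an assumption.

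**A reader might infer that a significant result is expected whenever patients improve on their own.** The figures do not support that. At 0.3 SD the chance is 25%, so a non-significant result is three times as likely. Section 2.2.1 also admits participants who are already independent and may have little room to improve on the Katz index.

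**A reader might infer that the protocol plans a false conclusion, or that calling the study a pilot contradicts its aim.** Neither follows. Section 2.6 promises only to compare scores before and after, and there is no success criterion or decision rule. The pre-post pilot design is stated openly, and a pilot may look at preliminary change. The mismatch lies in the claim to establish effectiveness.

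**The missing onset window might be read as the main fault.** It is secondary. The window is open at both ends, and narrowing it would reduce background change without removing it.

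**The design is understandable.** Section 1.3 cites few local specialists and restricted access during the pandemic. That can justify a single-arm pilot, but not a causal aim attached to it.

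**Conclusion.** The aim and objectives claim something the design cannot deliver. This follows from the protocol's own sections and needs no outside figure: with one group and one assessment on each side of treatment, background change and treatment effect are not separable. The nominal 5% error rate applies to the hypothesis of no change over time. For the hypothesis of no effect of the exercises it holds only if background change is exactly zero.

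The size is conditional. Under assumed background improvement of 0.3, 0.5 or 0.8 SD of the change score, with a two-sided test and all 20 patients analysed, an ineffective programme reaches p<0.05 in 25%, 56% or 92% of trials. The documents do not say which value, if any, applies.

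A single-arm pilot is legitimate in itself. What must change is the effectiveness wording, because it governs the study's central conclusion.

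**What to change.** 1. In the abstract's study aim, Section 1 and Section 1.4, restate the aim as estimating the mean four-week change under the programme, with a 95% confidence interval, as pilot data for a controlled trial. State that a significant paired t-test will not be reported as evidence of effectiveness.
2. Record time since onset at baseline and use it descriptively only. In 20 patients without a control it cannot separate treatment from recovery, and the protocol should say so.
3. Do not rely on a second pre-treatment assessment as a substitute for a control unless the interval between the two baselines is comparable with the four-week treatment period. Otherwise the untreated change is not comparable with the treated change and may give false reassurance.

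If an effectiveness claim is essential, a concurrent control is needed, and the sizes above show that this would be a different and probably larger trial.

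The recommended changes cost some protocol wording and one baseline item. The sample, the intervention and the test stay as they are. The downside is a more modest claim. The changes should be made before enrolment, so that the claim is settled before results are known and time since onset is recorded at baseline for every patient.

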**Methods:**

Twenty volunteers between the age of 40-59 years old, diagnosed, and confirmed to be suffering from vestibular neuritis and vertigo will be used in this study. Gaze stability exercises will be performed while patients are in a seated position. Each exercise will last for 30 seconds and be done in phases that included; eyeball movement, saccadic eye movement, pursuit eye movement, vergence eye movement, and vestibular-ocular reflex exercise. Balance exercises will be performed in a standing position including both static and dynamic training with or without closing eyes. The following outcome measures for each participant will be assessed pre-and post-treatment after completing four weeks of intervention. They include; Arabic version of Activities-Specific Balance Confidence Scale (A-ABC scale), Berg Balance Scale (BBS), and Katz Index of Independence in Activities of Daily Living (Katz ADL). The findings will then be subjected to statistical methods and data analysis using the SPSS toolkit.

**Key words:** vestibular neuritis, gaze stability, balance exercise

# **1 Background Information**

Balance and stability are important components for daily activities. Individuals need appropriate posture and coordination of various body parts for them to perform basic movements needed when doing various activities. The body requires a strong balance to perform day-to-day activities such as walking up and downstairs, bending, as well as lifting things from the ground. Lack of this balance, which can occur because of ear infections, accidents, and aging, generally can result in decreased quality of life. Nichols-Larsen et al., (2016) mentioned that vestibular neuritis is the second most common cause of vertigo and patients are complained of balance disturbance after head movements. Most healthcare facilities as well as health fitness centers use exercises to improve balance and stability in patients with balance problems. Examples of such balance exercises include gaze stability exercises. This literature reviews the effectiveness of gaze stability with balance exercises in enhancing balance, activities of daily living and reducing the risk of falling among patients suffering from vertigo due to vestibular neuritis in Riyadh.

## **1.1 Overview of Gaze Stability Exercises**

According to Gaikward (2016), Gaze stability exercises are part of vestibular rehabilitation therapy exercises. The exercises have become part of healthcare plans for patients with vestibular dysfunction (Gaikward, 2016). The exercises aim at improving vestibular ocular reflex (VOR), visual acuity during head movements, as well as reducing vertigo and dizziness (Gaikward, 2016). The therapy also improves postural stability, hence improving the quality of life among those affected (Gaikward, 2016). This, in turn, helps the patients achieve their activities of daily living (Clendaniel, 2010). Gaikward also mentions that the therapy works by promoting and stimulating vestibular adaptation and substitution to various stimuli provided during the exercises. Horizontal and vertical head movements with a fixed vision on a certain target induce retinal slip, which in turn increases the gain of vestibular response (Gaikward, 2016). However, achieving sustained vestibular response requires repeated exercises. Thus, most gaze stability exercises are prescribed for a long duration to achieve this response. Commonly used prescription is about four to five exercises in a day (Gaikward, 2016). The total exercises should last for an average of thirty minutes.

## **1.2 Effectiveness of Gaze Stability Exercises**

There are several studies and researches on vestibular rehabilitation therapy. A systematic analysis of most of these studies shows gaze stability exercises to be effective in achieving balance and postural stability (Kundakci et al., 2018, p.8). A recent study by Roh and Lee (2019) found a positive correlation between vestibular rehabilitation therapy and the improvement of balance and stability. According to their results, dynamic postural stability among patients with balance problems significantly improved after providing gaze stability exercises twice per week for four weeks. (Roh and Lee, 2019). The researchers used various forms of gaze stability exercises, including, eyeball, pursuit, saccadic, and vergence eye movements as well as vestibular ocular reflex exercise (Roh and Lee, 2019). Thus, these exercises proved effective in reducing vertigo, dizziness, and achieving balance among those affected.

Vestibular rehabilitation therapy also improves the overall health status of affected individuals as well as increasing the quality of their life. Tsukamoto et al., (2015) found an improvement in the quality of life among twenty patients diagnosed with vestibular disease. The intensity of dizziness also improved among these patients, with postural stability and balance improving in more than eight percent of the patients (Tsukamoto et al., 2015). Thus, the negative impacts of various vestibular diseases, including vestibular neuritis, can be minimized by prescribing well-coordinated and supervised gaze stability exercises.

Khanna and Singh (2014) saw related findings in another study. However, according to their results, improvement in postural stability and balance requires repeated exposure to interventions for a significant duration. The duo provided gaze stability exercises for two consecutive days per week for a duration of six weeks (Khanna and Singh, 2014). The patients conducted the exercises three times per day with each session lasting for forty to sixty minutes (Khanna and Singh, 2014). Moreover, vestibular rehabilitation therapy to be more effective if two or more types of exercises can be combined during the interventions. Those who were receiving balance training in addition to gaze stability exercises had a significant improvement in their balance and stability compared to those receiving either of the two therapies alone (Khanna and Singh, 2014).

Although vestibular rehabilitation therapy is generally effective, some studies have shown a negative side of them. According to Luth et al., (2019), the therapy is only effective for a short term, hence making them less effective than conservative as well as medical therapy. According to the researchers, vestibular rehabilitation therapy works only for a maximum of three weeks (Luth et al., 2019). The findings in this study can limit the use of vestibular rehabilitation therapy, including gaze stability exercises in those with long-term disabilities. However, combining various forms of exercises may remove this weakness, hence making vestibular rehabilitation therapy an interesting area for future researches.

## **1.3 Vestibular Rehabilitation in Saudi Arabia**

There is a consensus among scholars over a recently published study that presents concise and well-researched investigations on vestibular rehabilitation therapy. The study discusses vestibular rehabilitation therapy and its positive effects on vestibular dysfunction patients. Furthermore, this study stresses Vestibular rehabilitation as an effective form of therapy in alleviating the symptoms of various vestibular diseases such as vestibular neuritis. The therapeutic exercises are beneficial in attaining post stability and improving balance in patients with balance issues (Macias JD, Massingale S and Gerkin RD, 2005).

However, studying the application of the combination of gaze stability and balance exercises to improve daily living activities in patients suffering from vertigo with vestibular neuritis in Saudi Arabia poses challenges since there is a lack of published data in the department of Saudi Arabia. There are a few qualified specialists in Saudi Arabia practicing VRT besides it is not commonly used in local physiotherapy departments. The pandemic of Covid 19- has made it difficult for patients to receive physical therapy services that enhance telerehabilitation role. Therefore, this research designs need to look for ways to overcome those limitations by integrating other forms of exercises such as gaze stability and balance exercises with vestibular neuritis patients through telerehabilitation.

According to the existing literature, vestibular rehabilitation therapy is effective in alleviating the symptoms of various vestibular diseases such as vestibular neuritis. The exercises are useful in achieving postural stability and improving balance among patients with balance issues. However, the studies have some limitations since most of the researchers did not follow up on their participants for long enough to ensure they had long-term remissions. Thus, there is an opportunity to conduct more studies to ascertain the effectiveness of gaze stability exercises including the quality of patients' life among Saudi population.

## **1.4 Objectives**

This literature aims to assess whether conducting gaze stability with balance exercises has an improvement influence on balance and reducing falling incidence. Moreover, to study the impact of applying combination of gaze stability and balance exercises to improve activities of daily living in patients suffering from vertigo with vestibular neuritis in Saudi Arabia.

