This intervention of gaze stability with balance exercises will be given as scheduled in the treatment plan (table 1) (Appendix 1) (Roh and Lee, 2019). It will be applied twice each alternative day with ten repetitions for a total treatment period of four weeks. Each session will last for 45-60 minutes. Rest interval is between two groups of exercises for five minutes. Warm-up and cool down for five minutes is applicable before and after completing the treatment session. The patients will be followed up weekly through tele rehabilitation under the supervision of the researcher.

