## **2.5 Outcome measures**

The following outcome measures for each participant will be evaluated before the commencement of treatment and at the end of four weeks of training. They include; Arabic version of Activities-Specific Balance Confidence Scale (A-ABC scale) to measure patient self-confidence for performing activities of daily living without losing balance. Permission has been granted from original author [name] by email to use the Arabic version of the ABC scale. It has proved its good reliability and validity and can be used with the Arab population's vestibular disorders (Alghwiri AA, Alghadir AH, Al-Momani MO and Whitney SL, 2015) (figure 2) (Appendix 3).

In addition, Berg Balance Scale (BBS) to evaluate static balance and fall risk in adult. It has shown good reliability and validity with vestibular patients too (Alghwiri AA, Alghadir AH, Al-Momani MO and Whitney SL, 2015) (figure 3) (Appendix 3).

Moreover, Katz Index of Independence in Activities of Daily Living (Katz ADL) to define problems in performing ADLs. It has demonstrated excellent validity and reliability to assess the ability to perform daily living activities independently in adult and older community-dwelling populations (Hopman-Rock M, van Hirtum, H, de Vreede P and Freiberger E, 2019) (figure 4) (Appendix 3).

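### The objective includes fewer falls, but falls are neither recorded nor analysed; the nearest measure is a BBS fall-risk score, so that part of the objective cannot be answered

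*Protocol*

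**What the plan says.** Section 1.4 (Objectives) sets out to learn whether "conducting gaze stability with balance exercises has an improvement influence on balance and reducing falling incidence", and then adds an aim on activities of daily living. Section 1 (Background Information) describes the falls aim differently, as "enhancing balance, activities of daily living and reducing the risk of falling among patients suffering from vertigo due to vestibular neuritis".

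The outcomes, listed in the Abstract and in section 2.5, are the Arabic ABC scale, the BBS and the Katz index. Each is taken before treatment and at the end of week 4. The only link to falls is the description of the "Berg Balance Scale (BBS) to evaluate static balance and fall risk in adult". Section 2.6 applies a paired t-test to the three scores and a correlation between variables.

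The design is a single group: "This research is experimental with Pre-post cohort design, Pilot clinical trial". The size is 20, and section 2.3 justifies it only by saying "The sample size is the same as previous studies". Section 2.4 adds that "The patients will be followed up weekly through tele rehabilitation under the supervision of the researcher".

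**The concern.** An objective needs a measure that can answer it. The incidence of falls calls for a count of falls over a known period of observation. The protocol plans no fall history, diary, count or fall-rate analysis. A statistical analysis plan cannot supply this later, because it cannot analyse events that nobody recorded.

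Two things are at stake. First, a stated objective would go unanswered, and a change in BBS might be over-read as a change in falls. Second, falls are a foreseeable harm in this setting. Section 2.2.1 admits patients with a BBS from 21, and section 2.4 has them do standing, marching and walking exercises, for which in the last two weeks "participants will do the same exercises with closing eyes". Sessions fall on alternate days, while the follow-up contact is weekly. A fall between contacts would be known only if someone asked, and the protocol does not say that anyone will.

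**Working it through.** **Step 1: objective against measures.**

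| Part of the objective (section 1.4) | Measure (section 2.5) | Analysis (section 2.6) |
| --- | --- | --- |
| Balance | BBS, A-ABC | Paired t-test on scores |
| Activities of daily living | Katz ADL | Paired t-test on scores |
| Incidence of falls | None; BBS is a fall-risk score | None |

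The third row has no measure and no analysis. This conclusion needs no assumption and holds at any sample size.

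**Step 2: would counting falls rescue the objective?** The protocol gives no fall rate, effect size, SD or power, so there is no figure of its own to reproduce. Inputs taken from it are n = 20 (section 2.3), four weeks of treatment (section 2.4) and a 0.05 significance level (section 2.6; two-sided is my assumption). All 20 are assumed to be observed throughout.

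- Exposure: 20 × 4 = 80 person-weeks; 80 / 52.18 = 1.53 person-years.
- Expected falls = 1.53 × rate. At an assumed 0.5 per person-year this is 0.8; at 1, 1.5; at 2, 3.1; at 3, 4.6.

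**Step 3: a hypothetical before-after test.** Suppose falls were also counted, in the same way, for four weeks before treatment. Given the total, the split between two equal periods is binomial with probability 0.5 if nothing changes. The most favourable split is k falls before and none after, with two-sided p = 2 × 0.5^k:

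- k = 5: 2 × 0.03125 = 0.0625, not significant.
- k = 6: 2 × 0.015625 = 0.031, significant.

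At least six falls before treatment are therefore needed, even if falls then stop completely. With Poisson counts:

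| Assumed falls per person-year | Expected falls before | Chance of 6 or more before | Power to detect halving |
| --- | --- | --- | --- |
| 1 | 1.5 | 0.5% | 0.2% |
| 2 | 3.1 | 9% | 2.4% |
| 3 | 4.6 | 31% | 5.9% |
| 6 | 9.2 | 90% | 16% |
| 12 | 18.4 | >99% | 34% |

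Because the test against zero falls afterwards succeeds exactly when six or more occur before, the third column is also the power to detect complete abolition.

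**Step 4: the size that would be needed.** For 80% power to detect halving, on the log rate ratio with λ = rate × 4 / 52.18 falls per patient per period: N = (1.96 + 0.84)² × (1/λ + 1/(0.5λ)) / (ln 0.5)². At 2 falls per person-year, λ = 0.153 and N is about 320; at 1 per person-year it is about 640; at 12 it is about 54. With 20 patients, 80% power for halving needs about 32.5 falls per person-year, which is about 2.5 falls per patient in four weeks.

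**The case against.** The strongest reply is that this is a slip of wording. Section 1 speaks of the risk of falling, section 2.5 says the BBS evaluates fall risk, and the Abstract's study aim does not mention falls. Read together, the falls component has an instrument, and the word for incidence in section 1.4 is the outlier. Much of this stands. It shows how to resolve the conflict, and it means that section 1 needs no correction. It does not remove the conflict, because section 1.4 still promises something the plan does not measure.

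Two stronger readings are tempting and should be resisted.

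- *A trial of this size could never show a reduction in falls.* That depends on a rate the protocol does not give. At an assumed 6 falls per person-year, complete abolition would have about 90% power, and very frequent fallers would also be an exception. Very unlikely, at the assumed 0.5 to 2 per person-year, is as far as the figures go. For a pilot, low power for an event it does not measure is in any case a secondary matter.
- *A rise in BBS will be reported as fewer falls.* Nothing in the protocol says so; section 2.6 commits only to comparing scores. Over-interpretation is a risk, not a plan.

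It can also be said that recording falls as a harm is a separate matter from the objective, and that section 2.2.1 excludes people who cannot follow instructions or depend completely on an assistive device. Both are fair. Neither the exclusions nor the weekly supervision amounts to recording falls, and the same few questions serve the safety need.

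**Conclusion.** The point holds as an internal contradiction: section 1.4 names the incidence of falls, while the Abstract and sections 2.5 and 2.6 cover only A-ABC, BBS and Katz ADL. That part of the objective is unanswerable as designed, whatever the sample size.

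The numerical part is supporting and conditional. It rests on an assumed rate of 0.5 to 2 falls per person-year, Poisson counts, complete follow-up and a two-sided test. Within that range the power to detect halving is at most 2.4%. Even an observed drop could not be credited to the exercises, because there is no control group.

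**What to change.** 1. In section 1.4, replace *reducing falling incidence* with *change in fall risk as scored by the BBS*. This agrees with sections 1 and 2.5. Leave section 1 as it is, and state that no conclusion about the number of falls will be drawn.
2. In sections 2.4 and 2.5, add to each weekly tele-contact a question on falls, injurious falls and falls during the exercises since the last contact.
3. In section 2.6, state that these counts are reported descriptively as safety data only, with the number of patients and weeks observed. They should not become a before-after comparison: four-week recall at baseline, if it were added, would ascertain falls differently from weekly questioning.

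This must be in place before the first patient starts, because falls not asked about at the time cannot be recovered reliably. The cost is a changed phrase, a few extra questions in a contact that already takes place, and slightly more data entry. The exercises, eligibility and sample size are not touched.
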